## Abstract

**Background:**

Despite the positive impact of implantable cardioverter defibrillators (ICDs) and wearable cardioverter defibrillators (WCDs) on prognosis, their implantation is often withheld especially in Japanese heart failure patients with reduced left ventricular ejection fraction (HFrEF) who have not experienced ventricular tachycardia (VT) or ventricular fibrillation (VF) for uncertain reasons. Recent advancements in heart failure (HF) medications have significantly improved the prognosis for HFrEF. Given this context, a critical reassessment of the treatment and prognosis of ICDs and WCDs is essential, as it has the potential to reshape awareness and treatment strategies for these patients.

**Methods:**

We are initiating a prospective multicenter observational study for HFrEF patients eligible for ICD in primary and secondary prevention, and WCD, regardless of device use, including all consenting patients. Study subjects are to be enrolled from 31 participant hospitals located throughout Japan from April 1, 2023, to December 31, 2024, and each will be followed up for 1 year or more. The planned sample size is 651 cases. The primary endpoint is the rate of cardiac implantable electronic device implementation. Other endpoints include the incidence of VT/VF and sudden death, all‐cause mortality, and HF hospitalization, other events. We will collect clinical background information plus each patient's symptoms, Clinical Frailty Scale score, laboratory test results, echocardiographic and electrocardiographic parameters, and serial changes will also be secondary endpoints.

**Results:**

Not applicable.

**Conclusion:**

This study offers invaluable insights into understanding the role of ICD/WCD in Japanese HF patients in the new era of HF medication.

## INTRODUCTION

1

The effectiveness of implantable cardioverter defibrillator (ICD) has been well established for both secondary prevention who experienced ventricular fibrillation/ventricular tachycardia (VF/VT), and primary prevention of sudden cardiac death (SCD) in patients with reduced left ventricular ejection fraction (HFrEF). Guidelines from organizations such as the Japanese Circulation Society (JCS), the American Heart Association (AHA), the American College of Cardiology (ACC), the Heart Rhythm Society (HRS), and the European Society of Cardiology (ESC) recommend ICD implantation at class IIa or higher for eligible patients.^1^, ^2^, ^3^ Additionally, for HFrEF patients with a wide QRS on their electrocardiogram and left ventricular ejection fraction (LVEF) less than 35%, the prognostic impact of cardiac resynchronization therapy pacemaker (CRT‐P) and CRT defibrillator (CRT‐D) has become evident^4^, ^5^, ^6^, leading to similar recommendations of class IIa or higher for implantation as outlined in the guidelines of organizations such as JCS, AHA, ACC, the Heart Failure Society of America (HFSA), and ESC.^1^, ^7^, ^8^

Nevertheless, underuse of ICD has been reported especially in Asia including Japan.^9^, ^10^ Several factors contribute to this underutilization, including physicians' awareness, patients' consciousness, and various social factors, such as those associated with aging and economic considerations in Japan.^11^, ^12^, ^13^, ^14^, ^15^, ^16^ However, in recent years, studies undertaken in Japan, such as the HINODE trial, have shown mortality rates and rates of ventricular arrhythmias as high as those in Western countries.^17^ It has attracted attention to the potential significance of ICD/CRT‐D implantation as a primary prevention in Japan.

In recent years, new standard medications such as angiotensin‐receptor‐neprilysin inhibitor (ARNi) and sodium‐glucose cotransporter 2 inhibitor (SGLT2i) also reduce fatal arrhythmias and SCD in heart failure (HF) patients.^18^, ^19^ Furthermore, the effectiveness of wearable cardioverter defibrillator (WCD) has been demonstrated in high‐risk patients with structural heart disease who do not meet the criteria for ICD implantation (within the first 3 months after starting drug therapy).^20^, ^21^ However, the use of WCD also has not gained widespread acceptance in Japan. The evidence for ICD, CRT‐P, CRT‐D, and WCD was established in an era when there were no new HF standard medications. Based on the accumulation of evidence in Japanese people after the introduction of new HF medications, we believe it is a timely moment to reevaluate the significance of using these devices for HFrEF cases and high‐risk cases of VF/VT. Therefore, the purpose of this study is (1) to investigate the real‐world device implantation rates in HFrEF patients who meet the criteria for receiving an implantable device, including ICD, CRT‐D, CRT‐P, and WCD and (2) to compare characteristics and clinical outcomes between patients with and without device implantation.

## METHODS

2

### Study design and setting

2.1

The study will be based on TRANSITION JAPAN‐ICD/WCD, a large‐scale, multicenter, prospective registry including three types of HFrEF patients eligible for ICD for primary or secondary prevention of SCD, or WCD in Japan. Enrollment began on April 1, 2023, and the inclusion is planned to end on December 31, 2024, with all patients enrolled being followed up for at least 1 year (with the final follow‐up occurring on or before December 31, 2025). 31 institutions in Japan are participating in the registration (supplemental Figure S1). A flow diagram illustrating the overall follow‐up period and data analysis for the TRANSITION JAPAN‐ICD/WCD study is presented in Figure 1.

**FIGURE 1 joa313028-fig-0001:**
[figure not shown]
Flow diagram of the TRANSITION JAPAN‐ICD/WCD study.

### Eligibility and non‐eligibility

2.2

This study focuses on HFrEF patients who meet the criteria for receiving ICD for primary and secondary prevention of SCD and those who meet the criteria for WCD for primary prevention. Participants must be 20 years of age or older at the time of obtaining consent and provide written consent based on their own free will after receiving sufficient explanation regarding participation in this study. Patients eligible for this study will be basically fulfilled with the criteria of class I or IIa for ICD including sub‐cutaneous ICD (*S*‐*ICD*), and WCD as outlined in the JCS guidelines^1^: (1) patients with coronary artery disease (CAD) (≥40 days after myocardial infarction (MI) and at least 90 days after revascularization) or non‐ischemic cardiomyopathy who have NYHA class II or greater symptoms and an LVEF ≤35% despite optimal medical therapy, irrespective of whether they've experienced NSVT (criteria for primary prevention of SCD), (2) CAD or non‐ischemic cardiomyopathy who have NYHA class II or greater symptoms and an LVEF ≤35% accompanied by ventricular fibrillation (VF) or out‐of‐*hospital* cardiac *arrest* requiring electrical shock, sustained VT or unknown syncope, not due to reversible causes (criteria for secondary prevention of SCD), and (3) patients with LVEF ≤35% and HF symptoms of NYHA class II or III, and within 40 days after the onset of acute MI, and are within 90 days after coronary artery bypass or percutaneous coronary intervention, or within 90 days after the acute onset of HF due to a non‐ischemic etiology (WCD criteria). Therefore, this study will also include the patients who have opted not to receive ICD or WCD based on the patients' preference, including those without any cardiac device or those with CRT‐P. The following patients are excluded from this study: (1) those with a life expectancy of less than 12 months, (2) patients with frequent recurrent VT or VF that cannot be controlled with antiarrhythmic drugs or catheter ablation, (3) severe HF patients classified as NYHA class IV, (4) individuals unable to provide consent for the study, and (5) others judged unsuitable as study subjects by the principal researcher.

In short, the target cases for this study are those aged 20 or older with LVEF ≤35% and NYHA class II or higher HF symptoms despite adequate medical therapy, who do not fall under the exclusion criteria mentioned above.

### Study schedule

2.3

Patients diagnosed as eligible for ICD or WCD indications will start enrollment in this study when informed consent regarding their medical condition and treatment options is obtained. All items at the time of enrollment and follow‐up in both of patient groups eligible for ICD and WCD indications, are listed in Tables 1 and 2. The brief items include age, gender, height, weight, dairy habits, underlying heart disease, NYHA functional classification, medical history, Clinical Frailty Scale,^22^ medication history including HF treatment, the presence of atrial fibrillation/flutter or NSVT, history of revascularization or ablation for NSVT/VT, history of cancer, hemodialysis, echocardiographic parameters, simple electrocardiogram information, and laboratory data. For patient eligible for ICD indications, follow‐up items including laboratory data, echocardiographic and electrocardiographic parameters, NYHA classifications, Clinical Frailty Scale scores, and HF medications will also be collected again at 12 months after enrollment. For patients eligible for WCD indications, we will collect these follow‐up items at 3 months after enrollment, and again at 12 months thereafter. Simultaneously, we will monitor the observation items for at least 1 year, and until the final follow‐up period in cases followed up beyond 1 year, as in Tables 1 and 3. These include device introduction information, invasive treatments, and the occurrence of clinical events. After the observation period ending in December 2025, we will organize and analyze the data comprehensively by March 2026. Results of the study will be published in one or more peer‐reviewed journals by June 2026.

**TABLE 1 joa313028-tbl-0001:** Study schedule and main observation items.

Patient eligible for the indication of an ICD (including CRT‐D) Item(s) recorded		Registration	At 12 months after registration*	Final follow‐up
Patient information	Age, sex, height, weight, lifestyle habits, comorbidities, etc.	●		
	Electrocardiogram Echocardiogram	●	●	
	NYHA functional classification, Clinical Frailty Scale	●	●	
	Laboratory test results, medication information	●	●	
Observation items	Device implantation date (If not implanted, provide reason)			
	Invasive cardiac interventions			
	Clinical events (VT, VF, hospitalization for heart failure, cardiovascular death, etc.)			

Patient eligible for the indication of a WCD Item(s) recorded		Registration	At 3 months (corresponding to the time of WCD removal phase)	At 12 months after WCD removal phase*	Final follow‐up
Patient information	Age, sex, height, weight, lifestyle habits, comorbidities, etc.	●			
	Electrocardiogram Echocardiogram	●	●	●	
	NYHA functional classification, Clinical Frailty Scale	●	●	●	
	Laboratory test results, medication information	●	●	●	
Observation items	Device implantation date (If not implanted, provide reason)				
	Invasive cardiac interventions				
	Clinical events (VT, VF, hospitalization for heart failure, cardiovascular death, etc.)				

* Allowable range: within 3 months.

Abbreviations: NYHA, New York Heart Association; VF, ventricular fibrillation; VT, ventricular fibrillation.

**TABLE 2 joa313028-tbl-0002:** Basical registration items (patient information).

(1) At registration
Date of informed consent Age, gender, height, weight Smoking habits: Current/Former/Never Alcohol consumption: Daily / 2–3 times a week/Never Underlying heart disease (Ischemic cardiomyopathy/non‐ischemic cardiomyopathy [Dilated cardiomyopathy/hypertrophic cardiomyopathy/hypertensive heart disease/others]) NYHA functional classification (I/II/III/IV) Medical history (Diabetes, hypertension, dyslipidemia, ischemic heart disease [History of myocardial infarction/Angina], history of heart failure, chronic obstructive pulmonary disease, history of stroke, peripheral arterial disease) Clinical Frailty Scale: 1–9 Medication History ① Beta‐Blockers: Yes/No ② ACEi/ARB (angiotensin‐converting enzyme inhibitor / angiotensin receptor blocker): Yes/No ③ Mineralocorticoid Receptor Antagonists: Yes/No ④ ARNi (Angiotensin Receptor‐Neprilysin Inhibitor): Yes/No ⑤ SGLT2i (Sodium‐Glucose Cotransporter 2 Inhibitors): Yes/No ⑥ Ivabradine: Yes/No ⑦ Pimobendan: Yes/No ⑧ Digoxin Preparations: Yes/No ⑨ Antiarrhythmics: Sodium Channel Blockers (Procainamide/Disopyramide/Flecainide/Cibenzoline/ Pirmenol/Aprindine/Propafenone), Potassium Channel Blockers (Amiodarone/Sotalol/Bepridil) ⑩ Anticoagulants: Warfarin/Direct Oral Anticoagulants (DOACs) ⑪ Antiplatelet Agents: Yes/No ⑫ Lipid‐Lowering Medications: Yes/No ⑬ Diabetes Medications (excluding SGLT2i): Yes/No History of revascularization (percutaneous coronary intervention, coronary artery bypass grafting) Presence of atrial fibrillation/flutter (paroxysmal/persistent/permanent) Presence of NSVT (≥5 beats) History of ablation therapy for NSVT/VT History of cancer (gastrointestinal/lung/other) Dialysis (yes/no) Echocardiogram (LVEDV [mL], LVESV [mL], LVDd [mm], LVDs [mm], LAD [mm], LVEF [%], presence of moderate or severe valvular disease [MR, TR, AR, AS]) Electrocardiogram (heart rate, rhythm, QRS duration [ms], presence of ventricular pacing) Laboratory data (NTproBNP [pg/mL] or BNP [pg/mL], WBC [×10^9^/L], lymphocyte count [×10^9^/L], Hb [g/dL], Plt [×10^9^/L], BUN [mg/dL], Cr [mg/dL], eGFR [mL/min/1.73 m^2^], UA [mg/dL], AST [U/L], ALT [U/L], rGTP [U/L], Tcho [mg/dL], Na [mmol/L], K [mmol/L], TP [g/dL], Alb [g/dL], CRP [mg/dL]) Confirmation of performance only Signal‐averaged electrocardiogram (present/absent) Holter monitoring (present/absent) Cardiac MRI (present/absent)
(2) At 12 Months (±3 Months) (WCD indication group: at 3 Months corresponding to the time of WCD removal phase and 12 months after removal phase)
NYHA functional classification (I / II / III / IV) Echocardiogram (LVEDV [mL], LVESV [mL], LVDd [mm], LVDs [mm], LAD [mm], LVEF [%], presence of moderate or severe valvular disease [MR, TR, AR, AS]) Electrocardiogram (heart rate, rhythm, QRS duration [ms], presence of ventricular pacing) Labotatory data (NTproBNP [pg/mL] or BNP [pg/mL], WBC [×10^9^/L], lymphocyte count [×10^9^/L], Hb [g/dL], Plt [×10^9^/L], BUN [mg/dL], Cr [mg/dL], eGFR [mL/min/1.73 m^2^], UA [mg/dL], AST [U/L], ALT [U/L], rGTP [U/L], Tcho [mg/dL], Na [mmol/L], K [mmol/L], TP [g/dL], Alb [g/dL], CRP [mg/dL])

Abbreviations: AR, aortic regurgitation; AS, aortic stenosis; Alb, albumin; ALT, alanine aminotransferase; AST, aspartate aminotransferase; BNP, brain natriuretic peptide; BUN, blood urea nitrogen; CRP, C‐reactive protein; Cr, creatinine; eGFR, estimated glomerular filtration rate; Hb, hemoglobin; LAD, left atrial diameter; LVDd, left ventricular diastolic diameter; LVDs, left ventricular systolic diameter; LVEF, left ventricular ejection fraction; LVEDV, left ventricular end‐diastolic volume; LVESV, left ventricular end‐systolic volume; end‐systolic volume; MR, mitral regurgitation; NT‐proBNP, N‐terminal pro‐brain natriuretic peptide; NSVT, Non‐sustained ventricular tachycardia; NYHA, New York Heart Association; Plt, platelet; rGTP, γ‐glutamyltranspeptidase; Tcho, total cholesterol; TP, total protein; TR, tricuspid regurgitation; UA, uric acid; VT, ventricular tachycardia; WBC, white cell count.

**TABLE 3 joa313028-tbl-0003:** Observation items.

Observation Items (To be observed for a minimum of 12 months from the date of registration)
Device introduction For a case who are decided to receive no device implantation: Reasons for no introduction: (1) Patient does not want risk associated with implantation. (2) Patient does not believe in benefit of ICD/CRT‐D/WCD. (3) Patient unable to pay for device. (4) Other reasons. For a case of introduction: Date of device implantation, indication for device implantation (primary prevention / secondary prevention), type of device and product name (WCD/ICD/CRT‐P/CRT‐D/other), (new implantation/upgrading) For a WCD case, the date of removal Invasive treatments during follow‐up Date of invasive treatment, type of invasive treatment (implantable cardiac device/implantable loop recorder/catheter ablation/revascularization/device reoperation) Clinical event investigation Event Date ① Presence of VT (five or more consecutive beats), VF, and/or shock events (including inappropriate shocks) ② Presence of death (cardiovascular death, other causes of death: specify details) ③ Hospitalization due to heart failure ④ Other cardiovascular events requiring hospitalization ⑤ Stroke/TIA and systemic embolism ⑥ Myocardial infarction, unstable angina ⑦ Major bleeding (ISTH criteria) ⑧ Clinically significant bleeding

Abbreviations: CRT‐D, cardiac resynchronization therapy defibrillator; CRT‐P, cardiac resynchronization therapy pacemaker; ICD, implantable cardioverter defibrillator; ISTH, International Society on Thrombosis and Haemostasis; TIA, transient ischemic attack; VT, ventricular tachycardia; VF, ventricular fibrillation; WCD, wearable cardioverter defibrillator.

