### Primary and secondary endpoints

2.4

The primary endpoint is the rate of cardiac implantable electronic device implementation. The secondary endpoints are shown in Table 4. Other significant factors besides the primary endpoint include the incidence of VT/VF, the presence of sudden death, all‐cause mortality, and HF hospitalization, as well as other variables. We will gather standard clinical background information, each patient's Clinical Frailty Scale score, laboratory test results (including measures of nutritional status), and serial changes, which will also serve as secondary endpoints.

**TABLE 4 joa313028-tbl-0004:** Primary and secondary endpoints.

Primary endpoint	
Rate of cardiac electronic device implantation (ICD, CRT‐D, WCD, CRT‐P, or None)	
Secondary endpoints	
Occurrence of any of the following	
1. VT/VF and Sudden death^a^	
2. Death from any cause	
3. Cardiovascular events (stroke/TIA or systemic embolism, myocardial infarction/unstable angina, cardiovascular death [including sudden cardiac death], hospitalization for heart failure, or other cardiovascular event requiring hospitalization)	
4. Stroke/TIA or systemic embolism	5. Myocardial infarction/unstable angina
6. Heart failure requiring hospitalization or other cardiovascular event requiring hospitalization	
7. Major bleeding (ISTH criteria^b^)	8. Clinically significant bleeding
9. Major bleeding or clinically significant bleeding	10. Cardiovascular death
11. Other causes of death	12. Device‐related complications
13. Invasive cardiac interventions (surgery, catheter‐based treatments, pacemaker implantation, etc.)	
14. If patients refused implantation, reasons for ICD/CRT‐D/WCD implantation refusal (1. Patient does not want risk associated with implantation, 2. Patient does not believe in benefit of ICD/CRT‐D/WCD, 3 Patient unable to pay for device, or 4 Other reasons)	
Change in the following from the time of enrollment to 1 year (WCD cases: at the time of WCD removal and 12 months after removal):	
1. NYHA (New York Heart Association) functional classification, Clinical Frailty Scale	
2. Echocardiographic measures	
3. Hemoglobin, hematocrit, creatinine, NT‐proBNP or BNP	
4. Nutritional status markers (serum albumin concentration, white blood cell count [peripheral blood lymphocyte count], total cholesterol, C‐reactive protein)	

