### Statistical analysis

2.6

Continuous variables will be presented as mean ± SD or median (25th, 75th percentile) values and categorical variables as the number (%) of patients. Between‐group differences in continuous variables will be analyzed by unpaired *t*‐test or Mann–Whitney U‐test, and between‐group differences in categorical variables will be analyzed by chi‐squared or Fisher's exact test. Serial changes in NYHA, Clinical Frailty Scale, Echocardiographic parameters, and biomarkers will be evaluated by paired *t*‐test. We will examine device introduction rates, especially focusing on the ICD (CRT‐D) implantation as primary prevention, and compare patient characteristics between the ICD/CRT‐D group and non‐ICD (no device/CRT‐P) group. We will investigate the distribution of reasons for ICD/CRT‐D/WCD implantation refusal. Patients eligible for a WCD indication, whether they are using a WCD or not, undergo evaluation for primary prevention ICD eligibility within the first 3 months after registration. If they meet the primary prevention ICD criteria at 3 months after registration, they are categorized as those eligible for ICD primary prevention indication. However, a subset of patients does not meet these criteria and is categorized as the “no ICD indication” group. We expect that most patients will fall into this “no ICD indication” group, and we will investigate and clarify the characteristics of these patients among those eligible for a WCD indication.

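### Table 3 asks for a reason only when no device is placed, so a CRT-P recipient who declined a defibrillator falls inside the refusal endpoint but has no field for a reason

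*Protocol article*

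**What the plan says.** Table 3 (section 2.3) has two branches under device introduction. The first carries the reason list: "For a case who are decided to receive no device implantation: Reasons for no introduction", with four codes (implantation risk, disbelief in benefit, cost, other). The second covers patients in whom a device is introduced. It asks for date, indication and "type of device and product name (WCD/ICD/CRT‐P/CRT‐D/other", and adds "For a WCD case, the date of removal". It contains no reason item.

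Table 1 (section 2.3) has one panel for ICD-eligible and one for WCD-eligible patients. Both list "Device implantation date (If not implanted, provide reason" as an observation item.

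Elsewhere the question is about defibrillators, not about any device:

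- Section 2.2 includes patients who "opted not to receive ICD or WCD based on the patients' preference, including those without any cardiac device or those with CRT‐P".
- Table 4 item 14 (section 2.4) reads "If patients refused implantation, reasons for ICD/CRT‐D/WCD implantation refusal".
- Section 2.6 states "We will investigate the distribution of reasons for ICD/CRT‐D/WCD implantation refusal" and compares the ICD/CRT-D group with the "non‐ICD (no device/CRT‐P) group".

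Section 2.6 also says that WCD-eligible patients, wearers or not, are assessed for a primary prevention ICD within the first 3 months, and that those who qualify count as ICD-eligible.

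**The concern.** The condition for collecting a reason (no device) is narrower than the condition defining the endpoint (an ICD, CRT-D or WCD refused). Patients who meet the second but not the first are in scope with no data. CRT-P recipients are the clear case, because the protocol itself names them as having opted against a defibrillator.

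Exploring the reasons for refusal is among the aims stated at the start of the Discussion, which goes on to say that these reasons should inform patient education. CRT-P recipients have already accepted an implant, so their reasons for declining the defibrillator plausibly differ from those of patients who wanted no implant at all. Without them, the reported distribution describes only part of the non-ICD group whose characteristics and outcomes are analysed, and the share citing implantation risk may be too high. A reason that was never asked for cannot be recovered by any later analysis choice.

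**Working it through.** **Step 1. Follow each type of patient through the tables.** No formula applies here; the check is whether the collection rule and the endpoint agree.

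| Patient | Table 3 | Table 1 | Within Table 4 item 14? |
|---|---|---|---|
| Refused, no device | Reason asked | Reason asked | Yes |
| Took CRT-P, declined ICD/CRT-D | Introduction branch, no reason item | Implanted, so no reason asked | Yes |
| Wore WCD, met ICD criteria at 3 months, declined ICD | WCD is listed under introduction; only the removal date is added | Reason asked if implantation means an implant; not asked if it includes WCD | Yes |
| Declined WCD, later received ICD | Depends on whether the item is completed at the first decision or once overall | Implanted at the end; an earlier reason is not clearly requested | Yes, for the WCD |

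Row 2 is a mismatch under either table. Rows 3 and 4 turn on what implantation means. Table 4 lists WCD and CRT-P among the categories of its device implantation rate, so on that usage a WCD wearer counts as implanted. A WCD is worn, however, and the WCD panel of Table 1 runs from registration to final follow-up, so a wearer who never receives an ICD can equally be read as not implanted. The document does not settle which reading sites should use.

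**Step 2. Size, for the CRT-P group only.** Inputs from section 2.5: planned number 651, split 50% device and 50% non-implant. The target of 651 itself cannot be rebuilt, because the other institutions' survey counts are not shown, and nothing here depends on it.

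- Each half: 651 × 0.50 = 325.5, about 326.
- The CRT-P share of the device half, x, is not given. Assumed range: 5 to 15%.
- CRT-P patients: 325.5 × 0.05 = 16.3 and 325.5 × 0.15 = 48.8, about 16 to 49.
- As the two halves are equal, the share of the no-device plus CRT-P group without a reason is x/(1 + x): 0.05/1.05 = 4.8% and 0.15/1.15 = 13.0%.

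**Step 3. Effect on a reported share.** Suppose 40% of no-device patients cite implantation risk (an assumption; the document gives no figure) and a proportion p of CRT-P patients would do so. The share in the whole group is (0.40 + p·x)/(1 + x).

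- p = 0: 0.40/1.05 = 38.1% and 0.40/1.15 = 34.8%, so a reported 40% would become about 38% to 35%.
- p = 0.40: the share stays at 40%.

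These figures assume that every no-device patient supplies a reason and that every CRT-P recipient declined a defibrillator, as section 2.2 describes them. The number of WCD-cohort patients affected cannot be derived. Section 2.6 expects most of that cohort to have no ICD indication at 3 months, so only the remainder face the ICD decision.

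**The case against.** The strongest reply is that Table 3 is a condensed list in a journal article and not the case report form. It does not say that a patient takes one branch only once, or that an earlier reason is overwritten. Items are observed for at least 12 months, and the second reason code refers to the benefit of ICD, CRT-D or WCD without mentioning CRT-P, which suggests the authors had defibrillators in mind. Table 1 also asks for a reason when nothing is implanted, which can be read to cover a WCD wearer who never gets an ICD.

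Much of this stands for the WCD cohort, where the text is ambiguous and shows no definite loss. It does not remove the CRT-P problem. The article does not leave the trigger to another document; it states one, and that trigger differs from the endpoint. Table 1 does not help, because a CRT-P recipient is implanted.

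A reader might infer that CRT-P recipients and former WCD wearers are excluded from the refusal analysis. No section says so: Table 4 item 14 and section 2.6 place no such restriction. A reader might also extend the argument about accepted implantation risk to WCD wearers. They have accepted no implant and may well cite that risk, so leaving them out could shift the share the other way. A larger estimate that adds them to the CRT-P group and assumes none cites implantation risk is therefore not supported.

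**Conclusion.** The point holds for CRT-P recipients as a contradiction between the collection rule in Table 3 and the way sections 2.2, 2.4 and 2.6 define the refusal question. Followed as written, those who declined a defibrillator have no place for a reason. For the WCD cohort the finding is only that the tables leave it unclear whether a refusal at the 3-month ICD evaluation, or a WCD refusal followed by an ICD, is recorded.

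The true size is unknown. The illustration of 4.8 to 13.0% without a reason rests on an assumed CRT-P share of 5 to 15% of the device half. The shift from 40% to about 38% or 35% also needs the assumed 40% and the extreme assumption that no CRT-P recipient would cite implantation risk. One descriptive secondary endpoint is affected. The primary endpoint, the sample size and the event comparisons are not.

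**What to change.** In Table 3 and the case report form, trigger the reason item whenever an indicated ICD/CRT-D or WCD is not received, whatever other device is used. State explicitly that this includes CRT-P recipients, and WCD-cohort patients who meet the ICD criteria at 3 months and receive no ICD. Record which defibrillator each reason refers to, so that a WCD refusal and a later ICD decision in the same patient are both kept. Align the reason wording in Table 1 with this rule. Query sites for CRT-P and WCD patients already enrolled, and tabulate reasons for ICD/CRT-D and for WCD separately.

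The cost is one form change and some retrospective queries, whose answers will be less reliable than reasons recorded at the time. No visits or procedures are added.

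### The non-implant reason list cannot separate patient refusal from non-recommendation or loss of indication, and sudden death, device complications and haematocrit are endpoints without a dedicated data item.

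*Protocol article*

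**What the plan says.** **Reasons for no device.** Table 3 (section 2.3) puts the reason question to each case in which it was decided not to introduce a device. Table 1 likewise asks for a reason whenever no device is implanted, in both its ICD half and its WCD half. The list begins "Reasons for no introduction: (1) Patient does not want risk associated with implantation", continues with disbelief in the benefit, and ends "3) Patient unable to pay for device. (4) Other reasons". Endpoint 14 in Table 4 carries the same four codes under a narrower condition: "If patients refused implantation, reasons for ICD/CRT‐D/WCD implantation refusal". Section 2.6 announces a distribution of refusal reasons.

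**Sudden death.** Table 4 pairs it with VT/VF in secondary endpoint 1. A footnote defines it as a natural death that is instantaneous or follows the start of acute symptoms by no more than 24 hours, external causes excluded. Besides an event date, the death item in Table 3 reads "Presence of death (cardiovascular death, other causes of death: specify details".

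**Device complications.** Endpoint 12 in Table 4 is "Device‐related complications". The nearest entries in Table 3 are device reoperation, as a type of invasive treatment, and inappropriate shocks, inside the arrhythmia item.

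**Laboratory change.** Table 4 includes change in "Hemoglobin, hematocrit, creatinine, NT‐proBNP or BNP". Section 2.3 says that all enrolment and follow-up items "are listed in Tables 1 and 2".

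**The concern.** The article wants to explain why eligible patients go without a device. The Introduction says "Several factors contribute to this underutilization, including" and then names physicians' awareness before patients' outlook and social factors. The Discussion wants the reasons for refusal to inform patient education. If the form cannot distinguish a patient's refusal from a physician's decision or a lapsed indication, the table of reasons has no clear population. Its residual category then has no clear meaning, and the patient side is the only side reported in detail.

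Sudden death matters for a different reason. Section 2.6 uses VT/VF and sudden death for the Kaplan–Meier curves, the log-rank test and the propensity-matched hazard ratio between the ICD/CRT-D and non-ICD groups. A component that each of 31 sites classifies from its own free text may be ascertained unevenly. The unevenness could follow the comparison itself, because a patient without a device leaves no device recording of the terminal rhythm. That last step is my inference; the article does not say it.

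The complications and haematocrit gaps are smaller. They mean that two listed secondary endpoints have, respectively, partial and no support in the listed items.

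**Working it through.** The plan states no figure on this point, so the check sets each endpoint against the items printed to support it.

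1. **Who answers the reason question.** Tables 1 and 3: everyone without a device. Endpoint 14: refusers only. The second group is a subset of the first, and no field marks membership.
   - Codes 1 to 3 are the patient's risk aversion, disbelief in benefit and inability to pay.
   - Code 4 can hold a refusal for some other reason, a physician's non-recommendation, or an indication that no longer applies.
   - The number of refusers is therefore (codes 1 + 2 + 3) plus an unknown part of code 4. The denominator of endpoint 14 cannot be fixed, and neither can the content of its own residual category.

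2. **Whether non-refusal cases are expected.** Section 2.6 expects most WCD-indicated patients to be classed at 3 months as having no ICD indication. The WCD half of Table 1 still asks for a reason when nothing is implanted. No specific code fits a patient whose indication has lapsed.

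3. **How many patients the list covers.** Section 2.5 plans 651 patients, half without an implant: 651 × 0.50 = 325.5, or about 325. This is the number to whom the list applies, not the number misclassified.

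4. **Sudden death.** The definition needs the interval from symptom onset to death, and the cause. Table 3 prints an event date, a cardiovascular/other split and room for details. It prints no sudden-death category and no onset time. Classification is possible only where the details happen to contain the interval.

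5. **Device-related complications.** Reoperation captures complications that led to a further procedure, and inappropriate shocks are captured separately. A complication that led to neither has no dedicated place.

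6. **Haematocrit.** Table 2 lists haemoglobin at registration and at follow-up, and haematocrit at neither. With section 2.3 presenting Tables 1 and 2 as the full list of such items, this endpoint cannot be computed from what is listed.

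7. **Clinical Frailty Scale and medication.** Section 2.3 and Table 1 require both again at 12 months. The follow-up part of Table 2 omits both. Change in the Frailty Scale is a Table 4 endpoint.

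**The case against.** The best defence has four parts.

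- **The codes match.** Table 3 and endpoint 14 use the same four codes, and a residual code exists. A reader might infer that every non-implanted patient is recorded as a refuser. That is not so: a physician-driven case can go under code 4. What remains is that code 4 cannot be unpacked and the refusers cannot be counted.
- **Enrolled patients knew their options.** Section 2.3 starts enrolment once informed consent covering treatment options is obtained, and section 2.2 describes the patients without a device as having chosen so by preference. A reader might infer that a large share were never offered a device. The documents give no such share, and these two passages point the other way, so no count of misclassified patients is given here. They do not settle the matter: section 2.6 itself expects many WCD-indicated patients to end without an ICD indication, which is not a preference.
- **Sudden death may be recoverable.** The death item invites details, and Table 1 leaves its list of clinical events open-ended. The completeness statement in section 2.3 covers enrolment and follow-up items, not the events in Table 3. It would therefore be too strong to say that the endpoint cannot be delivered. The point is that no dedicated item is printed for a component of the main comparative outcome whose definition depends on timing.
- **An article condenses its case report form.** This carries weight for events. It carries little for the laboratory lists, which are detailed to the single analyte and described as complete. Haematocrit is nonetheless a minor endpoint, with haemoglobin collected at both times.

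The Frailty Scale and medication omission is an inconsistency between tables and not a loss of data, because Table 1 and section 2.3 both require them.

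**Conclusion.** The point holds in a limited form and deserves correction.

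- **Reasons for no device:** one list serves all patients without a device (about 325 if the planned split holds), while the analysis treats the answers as refusal. The refusal denominator is undefined and the residual code mixes different decisions. The size of the mixing is unknown.
- **Sudden death:** no dedicated category or onset time. This is the most consequential of the missing items because it enters the ICD versus non-ICD comparison. Some cases may be classifiable from free text.
- **Device-related complications:** partial proxies only.
- **Haematocrit:** not obtainable from the listed items. This is the only endpoint of which that can be said outright.
- **Frailty Scale and medication at 12 months:** a table to be aligned.

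The primary endpoint, the device implantation rate, is not touched. The verdict assumes that the printed tables reflect the case report form. If the form already carries these fields, the remedy is to say so and correct the tables.

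**What to change.** 1. Add to Table 3 an item with three answers: refused by the patient, not recommended by the physician, no longer indicated. Give the second answer its own reason codes, such as age, frailty or comorbidity, expected or observed recovery of LVEF, or another medical reason.
2. Restrict endpoint 14 and the matching analysis in section 2.6 to patients recorded as having refused. Report the other two answers as separate categories.
3. Add a sudden-death classification with time of symptom onset, time of death and witnessed yes/no, so that the footnote definition is applied the same way at all sites.
4. Add a device-complication item.
5. Add haematocrit at registration and follow-up, or delete it from Table 4.
6. Add the Clinical Frailty Scale and medication to the follow-up part of Table 2.

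The cost is a few form fields and a short chart query for patients already registered. Some onset times will not be recoverable; those deaths should be reported as unclassifiable, by device group. The query is best made while records and site staff are still accessible, since symptom timing and who made the decision are hard to reconstruct later.
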